## Abstract

**Background:**

Indigenous Australians suffer a disproportionate burden of preventable chronic disease compared to their non-Indigenous counterparts – much of it diet-related. Increasing fruit and vegetable intakes and reducing sugar-sweetened soft-drink consumption can reduce the risk of preventable chronic disease. There is evidence from some general population studies that subsidising healthier foods can modify dietary behaviour. There is little such evidence relating specifically to socio-economically disadvantaged populations, even though dietary behaviour in such populations is arguably more likely to be susceptible to such interventions.

This study aims to assess the impact and cost-effectiveness of a price discount intervention with or without an in-store nutrition education intervention on purchases of fruit, vegetables, water and diet soft-drinks among remote Indigenous communities.

**Methods/Design:**

We will utilise a randomised multiple baseline (stepped wedge) design involving 20 communities in remote Indigenous Australia. The study will be conducted in partnership with two store associations and twenty Indigenous store boards. Communities will be randomised to either i) a 20% price discount on fruit, vegetables, water and diet soft-drinks; or ii) a combined price discount and in-store nutrition education strategy. These interventions will be initiated, at one of five possible time-points, spaced two-months apart. Weekly point-of-sale data will be collected from each community store before, during, and for six months after the six-month intervention period to measure impact on purchasing of discounted food and drinks. Data on physical, social and economic factors influencing weekly store sales will be collected in order to identify important covariates. Intervention fidelity and mediators of behaviour change will also be assessed.

**Discussion:**

This study will provide original evidence on the effectiveness and cost-effectiveness of price discounts with or without an in-store nutrition education intervention on food and drink purchasing among a socio-economically disadvantaged population in a real-life setting.

**Trial registration:**

Australian New Zealand Clinical Trials Registry: ACTRN12613000694718

## Background

Indigenous people living in very remote communities in Australia have the poorest health outcomes of any population group in high income countries [1,2]. This burden of disease is in a large part due to poor nutrition across the life-course and is causing serious illness in what should be the most productive years of life. High food costs and generally low socio-economic status support a diet characteristically high in refined cereals, sugar and low in fruit and vegetables [3]. While efforts by individual communities and the Australian government to address food affordability and improve diet in this setting continue, there is little evidence on the effectiveness of different strategies.

There is compelling evidence that increasing fruit and vegetable intake and reducing sugar-sweetened soft-drink consumption can reduce the risk of preventable chronic disease. It has been estimated globally that an increase of 80 g per day of fruit and vegetables could reduce the risk of ischaemic heart disease by 10%, ischaemic stroke by 6%, lung cancer by 4% and oesophageal cancer by 6% [4]. Such an increase in fruit and vegetable intake in Australia could save approximately AUD157 million per year from the costs of cardiovascular disease (CVD) alone [5]. The benefits for the Indigenous population living in remote Australia are likely to be much greater considering their currently low intake of fruit and vegetables [3] and high burden of disease [1].

We have reported high consumption of sugar-sweetened soft-drinks in three remote communities of 474 ml (SD 51) per person per day on average [3]. Consumption of ≥ 1 serve of sugar-sweetened soft-drink per day (360 ml) has been associated with a higher prevalence of obesity among middle-aged women [6] and a reduction of one serving per day has been associated with a weight loss of approximately 0.5 kg at six and 18 months [7]. There is also the possibility that high fructose (the major sugar in many sugar-sweetened soft-drinks) intake is a direct risk factor for metabolic syndrome and Type 2 diabetes [8], which are highly prevalent in remote Australian Indigenous populations [9,10].

This evidence indicates that gains in health outcomes for Indigenous Australians living in remote communities could result from a shift in current consumption patterns, particularly in fruit and vegetables and sugar-sweetened soft-drink. There is growing evidence that taxes and discounts on food and beverages could influence consumption patterns considerably, and thus improve health outcomes [11-14]. Improved affordability has been associated with significant increases in the purchase and consumption of healthier foods [14,15].

Evidence from price discount studies suggests that demand for fruit-and-vegetables is price elastic – a 1% decrease in price is associated with more than a 1% increase in demand [14]. Waterlander et al. showed that a 50% discount on fruit and vegetables increased fruit and vegetable purchasing by a factor of four [16] and Ni Mhurchu et al. in a study conducted with supermarkets in New Zealand (NZ), showed a 10% increase in fruit and vegetable purchasing with a 12.5% price discount on healthy food options (the equivalent of removal of the NZ Goods and Services Tax) [13]. An et al. reported that 10% and 25% discounts on healthier food purchases were associated with an increase in daily fruit/ vegetable intake by 0.38 and 0.64 servings respectively [11]. There is little such evidence for socio-economically disadvantaged populations. The one study to date that has examined the differential price discount on food purchases across socio-economic groups, showed no variation in intervention effect by household income or education [17].

No studies, other than the SHELf study that is currently being conducted in Melbourne, Australia, have examined the cost effectiveness of price discount interventions [18] and little is known about the impact of subsidies on the overall diet and possible unintended consequences on diet[14]. A study conducted among urban poor households in two provinces in China demonstrated that reducing the price of a staple food commodity did not lead to an increase in demand for that commodity as people were able to purchase other foods that were highly valued but not necessarily of higher nutritional value [19]. This may not be the case however for households in high income countries. Ni Mhurchu et al., reported no change in purchase of less healthy foods and overall expenditure with a price discount on healthy foods [13]. Similarly Waterlander et al., reported no change in total expenditure, expenditure on non-food items or non-fruit and vegetable food items with a 50% price reduction on fruit and vegetables [16]. This uncertainty and lack of evidence however has impacted on policy adoption of economic incentive to improve diet [14].

It is posited that intervention to improve population diet needs to involve approaches that both target the individual and create an environment that supports individual food choice [20]. Nutrition education (targeting the individual) is frequently used to encourage healthy food purchasing, however the evidence for nutrition education impacting on healthy food purchasing is largely inconclusive [14]. Waterlander et al. showed no effect on fruit and vegetable purchasing with nutrition education alone (i.e., through provision of recipe books and telephone counselling) but reported an added beneficial effect when combined with a 50% price discount [16]. Ni Mhurchu et al. reported that tailored nutrition education, that suggested substitution of purchased unhealthy foods with specific healthier options, had no evident effect on the amount of purchased foods [13]. An et al. reported mixed results for nutrition education strategies using product labelling, promotional signage, stimulation (i.e., a text to remind/encourage action) or health messages (i.e., a text message to introduce health benefit of nutritious food intake) [14]. The benefit of combining a skill building nutrition education intervention (that develops budgeting, shopping and cooking skills), with a price discount, is being investigated as a means to improve dietary intake by the SHELf study in Melbourne, Australia [18].

Although consumers globally are driven by price, taste and convenience [21], the context of remote Australian communities is distinctive in the array of geographic, social, cultural and economic factors at play in determining food choice [22]. Remote Australian communities are largely dependent on an imported food supply. There are approximately 175 stores, each servicing populations of over 100, operating in remote Indigenous communities in Australia [23]. The community store provides much or most of the local food supply [24,25]. The food distribution chain for many remote Indigenous communities extends over thousands of kilometres and is vulnerable to disruption by seasonal weather conditions and associated events such as extended road closures [26]. In some cases food delivery is only by fortnightly barge and/ or aircraft [23]. These are factors which drive the price of food up to almost 50% higher than that in metropolitan centres [27].

The history of food supply systems is likely to have a continuing influence on food supply and purchasing patterns. It was not until the late 1960s and early 1970s, after dismantling of a government ration system and introduction of a cash economy, that Aboriginal people in remote communities had the means to independently purchase their food. In the early days of the community “trade store”, the range of food was very limited with few perishables and fresh produce available, unless grown or hunted and collected locally. Access to a wider range of foods has increased with improved transport routes and infrastructure and increasing consumer demand. Living conditions for residents of these communities have had a similar slow development, with overcrowding common and many houses and household infrastructure important to food preparation sub-standard and in a state of disrepair [28]. The history of poor access and uptake of to formal education has resulted in low literacy and educational levels, which also impact on opportunities for exposure to nutrition education and promotion, and lack of employment opportunities contribute to maintaining community income at a generally low level [2].

Despite these challenges, remote communities have good potential to positively influence dietary patterns, due to their relative size, collective sense of community, strong historical traditional structures of authority, and store ownership arrangements [26]. Improvements in biochemical dietary markers and reduced risk in cardiovascular disease have been demonstrated in two remote Aboriginal Australian communities in association with community-led initiatives which included improving the availability of healthy food in the store and providing individual level feedback on health status and dietary messages [29,30]. Similar initiatives have occurred in the remote community setting to promote healthy eating, including store shelf-talkers, cooking demonstrations, and removal of top selling sugar sweetened beverages [31]. The effect of these however on purchasing is largely not documented.

Further to these community-level initiatives, the Australian government instigated a community store licensing regime in 2007 in the Northern Territory (NT), where stores must demonstrate compliance with a set of minimum standards which include stocking of a range of essential food items, a pricing policy, and retail practices that support healthy eating [32]. This has resulted in tighter government control over retail operating practices in largely non-competitive environments where historically greater opportunity for consumer exploitation existed. The two major not-for-profit NT store associations (the Arnhem Land Progress Aboriginal Corporation (ALPA) and Outback Stores (OBS)) servicing in total 38 of the around 90 remote stores in the NT have also instigated various food subsidy strategies to reduce the cost of healthy food [33,34]. Currently ALPA applies a no freight charge to fresh fruit and frozen, tinned and dried vegetables, fresh milk, yoghurt and cheese. Similarly, OBS does not apply a freight component to fresh fruit and vegetables and since 2010, has made bottled water available at a reduced price in all its stores. Similar initiatives have been instigated by some independent store operators and other store associations in remote Indigenous Australia.

Despite such nutrition-related initiatives occurring in remote Indigenous Australia, most are not evaluated or designed to provide robust evidence of effect. This has contributed to the paucity of evidence about the most effective means of supporting healthy eating behaviour. The inferior health of Indigenous Australians relative to other Australians, and the role of poor nutrition in the health disparity presents a compelling reason to identify cost-effective interventions for nutrition improvement. This study provides the opportunity to examine the effectiveness and cost-effectiveness of evidence-based strategies that have the potential to positively influence food and drink purchasing in the context of a socio-economically disadvantaged population.

### Study aim

The study tests the hypothesis that, over a six-month intervention and at six-months post-intervention, there will be a beneficial impact of (i) a 20% price discount and (ii) the addition of in-store nutrition education to the price discount intervention on the primary outcome measure of per capita daily weight (grams) of fruits and vegetables combined purchased through the community store, as well as on secondary outcome measures relating to the purchase of food and beverages and to the nutrient composition of purchased foods through the community store. The effect of the intervention will be measured via store point-of-sale data. In these remote communities where there is a single food store, point-of-sale data can provide a reliable and objective indicator of community level dietary intake [25,35]. A secondary aim of SHOP@RIC is to assess cost-effectiveness of the strategies to determine if the strategies represent good value-for-money in relation to disability adjusted life years (DALYs) saved over the lifetime of the community’s population. Overall food purchases and total diet/ energy intake will be assessed to document any unintended consequences of the strategies. An assessment of the influence of contextual factors, proposed mediators of behaviour change such as self-efficacy and perceived affordability of healthy food, and intervention fidelity will be conducted to aid interpretation of study findings and the understanding of mechanisms of behaviour change (Figure 1). This protocol relates to the primary aim of the study to assess effect of the price discount with or without the in-store nutrition education strategy on the primary and secondary outcome measures.

**Figure 1 F1:**
[figure not shown]
Study logic model.

## Methods

### Setting

Aboriginal and Torres Strait Islander people represent 2.5% of the Australian population [36]. Twenty-four percent of Indigenous people live in remote/ very remote areas of Australia in small settlements commonly referred to as communities and/or homelands. These communities vary in size from an extended family group to over 2500 people, with most having less than 1000 people. Very remote areas are defined by geographic distance which imposes a severe restriction on accessibility to a range of goods and services [37]. These communities are also considered to be socio-economically disadvantaged according to the Socio-Economic Indexes for Areas (SEIFA index) based upon aggregated social and economic information collected through the national Australian population census [38]. Indigenous people represent 30% of the NT population and 72% live in remote or very remote areas.

The NT covers an area of 1,352,176 square km (which is equivalent to France, Italy and Spain combined). The majority of stores in the NT are owned and controlled by the Indigenous community as not-for-profit organisations and are governed by a board of directors, generally referred to as a store committee [26]. These committees comprise community leaders and/or community elders. Commonly, a non-Indigenous manager is appointed privately or by a consultancy firm contracted to manage the store [26].

The proposed study represents a collaboration with the two major store associations in the NT, ALPA and OBS and the respective store-owners. In the NT, ALPA manages 16 stores and OBS manages 22 stores.

### Design

The SHOP@RIC study is a multiple baseline (stepped wedge) randomised trial [39,40]. Twenty consenting communities have been randomly grouped into sets of 4 communities. Because of the logistical difficulty of commencing the price discount intervention and nutrition education strategies simultaneously in all communities, each set of four communities was randomly allocated to initiate the intervention at one of five possible time-points (the first set commenced in June 2013), spaced two-months apart. A 20% price discount on fresh and frozen fruit and vegetables, water and diet soft-drinks will be applied for a period of six months in each of the twenty communities and co-exist with other food-related promotions that may occur during this period. All community residents will have access to the intervention. Half the communities (i.e., ten stores; approximately one ALPA and one OBS store in each of the five sets) have been randomly allocated to receive the combined intervention – price discount and in-store nutrition education strategy. The study will apply a six-month intervention and pre-, post-, and six-month follow-up assessments of intervention effect.

#### Process evaluation - intervention confounders, mediators and intervention fidelity

Descriptive data on potential covariates (referred to in Figure 1 as contextual factors – these include factors such as frequency of food delivery, population movement, functioning of store equipment, retail practice) will be collected weekly for all communities through a structured survey administered over the course of the study. A before-and-after sub-study among a cohort of 150 community members recruited from five communities (comprising one community receiving the combined intervention in each of the five store sets), will examine hypothesised mediators of intervention effect on self-reported intake of fruit, vegetables, water, diet soft-drinks and sugar-sweetened soft-drinks. Qualitative and quantitative methods will be used to assess intervention fidelity, including an assessment of dose, reach and barriers and enablers to implementation.

### Theoretical framework

The strategy is informed by social ecological theory that proposes that behaviour is shaped by interaction between the individual and the environment [41] and that health promotion therefore requires both behavioural (e.g. nutrition education) and environmental strategies (e.g. price discount). It is also guided by Social Cognitive Theory (SCT) that asserts that individuals adopt new behaviours through social learning which involves outcome expectancies (i.e., consideration of the consequences of actions), observational learning, self-efficacy (i.e., confidence in performing a behavior), behavioural capabilities (i.e., skills and knowledge), and reinforcement [42]. These mediators may intervene in the process of learning and behaviour change. An understanding of these mediators is important in determining the most successful intervention elements and how they operate to change behavior. Figure 1 provides an overview of the program logic that underpins the relationship between the intervention, co-variates (contextual factors and the mediators of behaviour change), intervention fidelity, and outcomes (combined fruit and vegetable purchasing and intake).

Ethical approval has been granted by the combined NT Department of Health and Menzies School of Health Research Human Research Ethics Committee (ref: HREC-2012-1711), the Central Australian Human Research Ethics Committee (ref: HREC-12-13) and Deakin University Human Research Ethics Committee (ref: HREC-2012243).

### Eligibility and recruitment

#### Recruitment of stores

Twenty community stores (twelve OBS stores and eight ALPA stores) met the following criteria and were invited to participate in the study:

– Community store managed by either ALPA or OBS

– Community located within the NT

– Store located more than 20 kilometres from its nearest competitor

– Community population of 100 residents or greater

Initial contact was made with a representative of each of the community store boards and information provided on the study. This contact was facilitated by OBS and ALPA personnel and either an OBS/ ALPA representative alone or together with a member/s of the research team, visited each community. A study “story” was used to faciliate a discussion with store board representatives and to ensure comprehensive understanding of the study and study protocol. Through this process, research agreements, outlining the responsibilities of all parties (ALPA/OBS, store owners and Menzies School of Health Research), were signed. Store-owners were asked to assist with the recruitment of community-based research assistants. These personnel will be trained to assist with all community-level study activities, and invited to participate in a workshop at the end of the study to interpret study findings and plan for research dissemination.

#### Recruitment of participants to sub-study for assessment of mediator measures

Approximately 40 adults will be recruited to participate in each of the five sub-study subset communities. It is expected that an initial sample of 40 will result in a final sample of at least 30, allowing for attrition over the study period (minimum of 150 from across five communities). On a visit to each household randomly selected to participate, an adult meeting the eligibility criteria (community resident, plans to reside in the community for 12 months, over 18 years, purchases food from the community store, and is the primary shopper) will be invited to participate in a survey and requested to provide written consent following explanation of purpose of the sub-study and of the interview. On completion of the survey at each of the three time points, a AUD20 gift of fruit and water will be provided to each participant. Feedback of key messages from the sub-study will be provided to participants at the end of the study, based on aggregated data.

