#### Process evaluation

An electronic survey tool has been developed to collect data from store managers and community key informants on factors identified by experts to influence food and beverage purchases including (Table 1):

• Store retail practices

• Community events or activities

• Population movement

• National or global events/ activities

Data on these factors will be collected for each of the study communities throughout the course of the study commencing in May 2013. Information on these contextual factors will be used to identify potential analytical covariates and to aid interpretation of impact of the intervention to the outcome measures. To examine proposed mediators of behaviour change, data will be collected on mediator measures and self-reported consumption of fruit, vegetables, water, diet soft drinks and sugar-sweetened soft drinks. These data will be collected pre- and immediately prior to the end of the intervention and at six-months follow-up, using survey items adapted from previously published scales [18] after extensive pilot-testing to make them more appropriate to the cultural context of the study population. Additional data will be collected to assess intervention i) fidelity; ii) dose and reach; and, iii) perceived barriers and enablers to implementation. This will involve the collection of observational data including in-store spot checks; documentation of activities implemented; and interviews with key stakeholders (including the store manager, store staff and key community informants). A summary of all study measures is shown in Table 1.

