### Analyses

#### Primary and secondary outcome measurements

Mixed models will be used to analyse the store point-of-sale data; random effects will include the store; fixed effects will include the step (of 8 weeks in length which corresponds to the “lag” in the roll-out of the intervention across sets of stores), the phase (baseline, intervention, post-intervention) and the in-store nutrition education strategy. Additional covariates (the contextual factors - such as distance to competing food outlet, community level income, population size) will be described and tested and may be introduced as additional fixed effects. It is expected that there will be some additional correlation within each store and a variance-covariance model (VCVM) for this will be identified prior to the formal testing of the fixed effects and other covariates. Mediation analyses will be undertaken using the MacKinnon method [47]. Descriptive statistics (for quantitative data), content and thematic analysis (for qualitative data) will be used as appropriate to analyse data on intervention fidelity. This information will be used to aid interpretation of results of the outcome measures.

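### The mediation survey runs only in combined-arm communities, so up to half of any effect of survey contact on store sales would be counted as an effect of nutrition education; one sensitivity analysis would separate the two.

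*Protocol article*

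**What the plan says.** The Design section states that half of the twenty communities "have been randomly allocated to receive the combined intervention – price discount and in-store nutrition education strategy". The process evaluation paragraph of the same section places the sub-study in five communities, "comprising one community receiving the combined intervention in each of the five store sets".

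The sub-study recruitment section states "Approximately 40 adults will be recruited to participate in each of the five sub-study subset communities". Participants come from randomly selected households and must be adults for whom it holds that each "purchases food from the community store, and is the primary shopper". It adds: "On completion of the survey at each of the three time points, a AUD20 gift of fruit and water will be provided to each participant". On timing, the process evaluation paragraph under Data collection says "These data will be collected pre- and immediately prior to the end of the intervention and at six-months follow-up". Table 1 lists what the interviews cover: perceived affordability and benefits of fruit and vegetables, self-efficacy, barriers, and intake of the targeted foods and drinks.

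The sales model under Analyses has a random store effect and fixed effects for step, "the phase (baseline, intervention, post-intervention) and the in-store nutrition education strategy". Further covariates may be added, but those described are contextual factors. Sub-study participation is not among them.

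**The concern.** Whether education adds to the discount is part of the primary hypothesis, and the Sample size section powers it separately. The survey reaches main shoppers who use the study store, asks about the behaviours that the education strategy targets, and takes place only where education is given. The education contrast therefore compares education with survey (five stores) and education without survey (five stores) against neither (ten stores). If being interviewed changes what people buy, part of that change is credited to education, and the test of education rejects too often when education does nothing. The Blinding section considers how lack of blinding may affect self-reported intake, but does not discuss whether the survey could affect store sales.

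**Working it through.** **Inputs from the Sample size section.** Log-scale residual SD 0.16; between-store SD 0.48; 20 stores; 8-week periods; data used to the end of the intervention; effect of interest log(1.20) = 0.1823.

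**Inputs from Design.** Five sets of four stores, starting two months apart; six months of intervention, taken as three periods.

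**Assumptions.** Two combined and two discount-only stores in every set; a two-sided 5% test; five baseline periods before the first set starts (37 weeks of baseline data are mentioned, and 37/8 = 4.6).

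**1. Reproducing the stated power.** Generalised least squares for this model gives SE(education) = 0.0495 and SE(discount) = 0.0529.
- Education: Φ(0.1823/0.0495 − 1.96) = 95.8%, against about 97% stated.
- Discount: Φ(0.1823/0.0529 − 1.96) = 93.1%, against about 95% stated.

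Both are within two points, so the model is a fair copy. A hand check agrees. The sets have 5, 6, 7, 8 and 9 baseline periods, and the mean of 1/b is 0.149. A store's intervention-minus-baseline difference then has variance 0.16² × (1/3 + 0.149) = 0.01235. For ten stores against ten, SE = √(0.01235 × 2/10) = 0.0497.

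**2. Share absorbed by the education coefficient.** In each set, one of the two combined stores is surveyed. An effect acting at full strength in all three intervention periods has share 1/2 = 0.50, and the discount coefficient takes 0.00. Otherwise:
- first period only: 0.50 × 1/3 = 0.167;
- halving each period: 0.50 × (1 + 0.5 + 0.25)/3 = 0.292;
- last baseline period and first intervention period only: 0.09 from the model, because the baseline part offsets the rest.

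**3. Test size if education has no effect.** With δ = share × log(1 + survey effect), size = 1 − Φ(1.96 − δ/SE) + Φ(−1.96 − δ/SE).

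| Pattern | Survey effect on store sales | δ/SE | Apparent education effect | Test size |
|---|---|---|---|---|
| Persistent | 2% | 0.20 | +1.0% | 5.5% |
| Persistent | 5% | 0.49 | +2.5% | 7.8% |
| Persistent | 10% | 0.96 | +4.9% | 16.1% |
| One period | 5% | 0.16 | +0.8% | 5.3% |
| One period | 10% | 0.32 | +1.6% | 6.2% |
| Halving | 5% | 0.29 | +1.4% | 6.0% |
| Halving | 10% | 0.56 | +2.8% | 8.7% |

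Four or six baseline periods change these little: the persistent 10% case becomes 15.5% or 16.6%.

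**4. Reach.** Household size is not given. At an assumed 4 to 7 persons, 40 households hold 160 to 280 people. That is 32–56% of a community of 500 and 16–28% of one of 1000. The recruitment criterion is "Community population of 100 residents or greater", but 100 residents make only 14 to 25 such households, so 40 could not be recruited there on this assumption.

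**5. With a sub-study term added.** SE(education) rises to 0.0606 and power is Φ(0.1823/0.0606 − 1.96) = 85.3%. Hand check, five stores against ten: √(0.01235 × (1/5 + 1/10)) = 0.0609.

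**The case against.** The strongest objection is that nothing in the documents shows that interviews change purchasing. The Background points the other way: it reports no effect on fruit and vegetable purchasing from recipe books and telephone counselling alone, and no evident effect from tailored education. A questionnaire is a weaker contact than either. At 16–28% reach, a 5% rise in store sales would need surveyed households to buy about 18–31% more (5/28 to 5/16). This stands, and it is why the point concerns a possible bias of unknown size.

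Timing also limits the size. The second wave comes just before the intervention ends and the third at follow-up, so essentially one interview can act on the intervention-period contrast. The post-intervention contrast is more exposed to the later waves. A reader might infer that the first interview falls directly before the discount starts. The article says only that it is pre-intervention, and a reaction during baseline weeks would offset part of the bias.

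A reader might also infer that a positive result could not be assigned to education at all. That goes too far, because five combined communities are unsurveyed and supply a clean comparison. Nor does the survey cover the whole of the smallest communities, as the household arithmetic shows.

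Finally, a sensitivity model is something a journal article may leave to an analysis plan, and the covariate wording would permit it. That is fair. But the one-sided placement of the survey is a stated design choice, and the covariates described do not address it.

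**Conclusion.** The point holds in a limited form. The survey is confined to half of the combined arm, the named model cannot tell it from education in those stores, and the education coefficient takes up to half of any survey effect. The upper limit of one half requires a single interview to act at full strength through all three intervention periods; if the effect fades, the share is about 0.17 to 0.29, and lower still if part falls in baseline. Test size then ranges from barely above 5% to about 16% for assumed effects of 2% to 10%. These effects are illustrations, since the documents supply no estimate. The calculation also assumes an even split of arms within sets and five baseline periods. It does not count gift food: whether the gifts are bought through study stores is not stated. This is a cheap improvement to interpretation and does not undermine the main analysis.

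**What to change.** Pre-specify one sensitivity analysis that adds to the planned sales model a term for sub-study community, switched on from the start of the intervention phase. Education is then estimated from the five unsurveyed combined stores against the ten discount-only stores. State how the five communities were chosen within the combined arm, since that bears on how clean this contrast is, and when the first wave falls relative to the discount start.

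Run it only after the blinded main analysis is complete. The indicator exists only in combined stores, so it would reveal the education codes that the Blinding section keeps from the statistician.

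Report the estimate and its interval beside the main one, to inform interpretation. Do not make attribution to education depend on the two agreeing: their difference has SE √(0.0606² − 0.0495²) = 0.035, so a formal comparison would detect a persistent 5% or 10% survey effect with only about 11% or 28% power.

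Surveying discount-only communities equally is not a free alternative, because half of the survey effect would then move to the discount estimate.

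The cost is one extra model on data already held and a less precise secondary estimate (SE about 0.061 against 0.050; power for a 20% effect about 85% against 96%).
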